**Figure 2 F2:**
[figure not shown]
**Syndrome differentiation of meridians in headache region**.

1. Shaoyang headache (TE-GB): SJ5 (Waiguan), GB34 (Yanglingquan).

2. Yangming headache (LI-ST): LI 4 (Hegu), ST 44 (Neiting).

3. Taiyang headache (SI-BL): BL 60 (Kunlun), SI 3 (Houxi).

4. Jueyin headache (PC-LR): LR3 (Taichong), GB40 (Qiuxu).

5. Nausea and vomiting: PC6 (Neiguan).

6. Dysphoria and susceptibility to rage: LR3 (Taichong).

Needles are inserted 10–15 mm in depth and manually manipulated by rotation methods to produce a characteristic sensation known as "De Qi".

#### Sham Acupuncture

To make the quantity of stimulus uniform between two groups, the decision is made to use the same kind, size and number of needles for sham acupuncture as which are used in verum acupuncture. However, the sham points selected would be confirmed as the distant non-meridian points that are defined as 3 mm apart from the points without effects on headache. The procedure for developing the sham acupuncture protocol contains three steps:

1. Literature search: Based on the search and analyses of 26 Chinese acupuncture ancient articles, 3 Chinese acupuncture textbooks and more than one hundred acupuncture modern articles, the points with no reference to effects on headaches have been enumerated.

2. Point selection: To avoid the effects on headaches and the effects of alleviating pain, the points in the head, trunk, hands and feet are excluded. And then 30 points without effects on headaches are extracted and the locations 3 mm apart from these points are defined as sham points, which are used in the control group.

3. Sham points subgroup: 30 sham points are randomly assigned to five subgroups of control groups which are labeled from B to F and recorded in the predetermined computer-made randomization sealed envelope. Each subgroup has two points on arms and three points on legs. The patient who belongs to the control group will be assigned to one of subgroups and the five points in this subgroup will be used on this patient in the whole treatment period. The details of the sham points in the control group are in Table 1.

**Table 1 T1:** The sham points in the control group.

Subgroup	Code	Arm		Leg		
1	B	LI15†	LI14‡	KI9†	GB33†	LR7†
2	C	SJ6‡	SJ8†	SP7†	KI10†	GB38†
3	D	LI13‡	PC5‡	GB35†	GB37†	GB39†
4	E	LU5‡	PC2‡	SP9†	KI7†	LR6†
5	F	LI12‡	HT4‡	ST32‡	ST38‡	ST39‡

† Backward 3 mm from the point; ‡ Outward 3 mm from the point.

### Outcome measures

The efficacy of acupuncture for migraine prophylaxis is assessed by the following primary outcome measures:

1. Change in frequency and duration of migraine attacks [13].

2. The proportion of responders, defined as the proportion of patients with a reduction of migraine days by at least 50% [13].

3. Visual Analogue Scale (VAS) to assess the severity of migraine pain [17].

4. Short-Form of McGill Pain Questionnaire (SF-MPQ) [17,18].

The secondary outcome measures include:

1. The summary scales of the SF-36 [19,20].

2. Intake of acute-medication [13].

3. Number of patients with adverse side effects [21].

4. Change in the frequency of nausea and vomiting [22].

The outcome measures above will be assessed before the treatment, the week of the last acupuncture session and 12 weeks after the last acupuncture session.

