### Participants

One hundred and forty patients with migraine without aura enrolled in the trial are recruited from outpatient in acupuncture clinics of the five hospitals. The main inclusion criteria are: patients suffering from migraine without aura (more than 2 migraine attacks in 4 weeks), diagnosed according to diagnostic criteria of the International Headache Society [1]; male or female; aged 18–65 years; patients who had not used acupuncture or drugs with migraine prophylactic effects within the last 3 months; patients who have given written informed consent.

The main exclusion criteria are: tension-type headache, cluster headache and other primary headaches; secondary headache and other neurological diseases; neuralgia of the face or head; pregnancy, nursing mother or insufficient contraception; use of prophylactic migraine medication in the last 3 months; therapy with β-blocker in the last 3 months; intake of antipsychotic or antidepressant drugs; participation in another clinical trial; having family history of depression, Parkinson disease and other extra-pyramidal diseases.

According to the previous studies in China and our pilot study, we anticipate that the proportion of responders [13] (50% or greater reduction in attack frequency) would be 65% [14,15] in control group and 90% [16] in acupuncture group. Based on 0.9 power to detect a significant difference (α = 0.05, two-sided), 56 patients are required for each group calculated by EpiCalc 2000 Version 1.02. To compensate for dropout patients, we plan to enroll 70 patients per group.

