### Statistical analysis

All analyses will be done on the intention-to-treat group of participants who have been randomized regardless of whether they receive any treatment. Missing data will be replaced according to the principle of the last observation carried forward. A variance analysis reject the global hypothesis H_0_: "There is no difference in the success probability between two groups." The significant level used for the statistical analysis is 5%, therefore P < 0.05 indicates significance. Analysis of variance (ANOVA) for repeated measures is used to compare the two groups. Comparisons within groups for the outcomes in each one of the time point were done using the Tukey's post hoc test of Multivariate Analysis of Variance (MANOVA). In the case of proportions, a *chi-square test *is applied. Stratified analysis within five different centers will be performed to control confounding factor if necessary. All analyses are performed using the Statistical Package for the Social Sciences (SPSS) software program (version 13.0) for Windows XP.

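### Five primary variables at two post-baseline times are each tested at 5% with no single primary or success rule; if any one result counts as success, the false-positive risk is about 10% to 26%

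*Protocol article*

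**What the plan says.** Protocol article, Outcome measures: the list begins "The efficacy of acupuncture for migraine prophylaxis is assessed by the following primary outcome measures" and has four items. Item 1 covers both the frequency and the duration of attacks, item 2 the responder proportion (at least a 50% reduction, counted in migraine days), item 3 the VAS and item 4 the SF-MPQ. All outcomes are to be "assessed before the treatment, the week of the last acupuncture session and 12 weeks after the last acupuncture session", which gives two post-baseline times.

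Statistical analysis: "The significant level used for the statistical analysis is 5%, therefore P < 0.05 indicates significance". The two groups are compared by repeated-measures ANOVA, and proportions by chi-square at no stated time. An overall null hypothesis about the success probability is mentioned. Tukey's procedure is named for comparisons within groups.

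Participants: the trial is sized on a responder proportion that "would be 65% [14,15] in control group and 90% [16] in acupuncture group". The result is "Based on 0.9 power to detect a significant difference (α = 0.05, two-sided), 56 patients are required for each group", raised to 70 for dropout. Response is defined there as "50% or greater reduction in attack frequency".

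Procedures: endpoints are collected by blinded telephone interviewers 16 weeks after randomization, to evaluate the long-term effect. That time is not called primary.

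**The concern.** When several outcomes share the label primary and each is tested at the full 5% level, the trial has several chances to produce a significant primary result by luck. The protocol does not say whether one, some or all must succeed, or at which visit. A single favourable result could then be reported as success on a primary outcome, and the 5% rule would support calling it significant. A mixed set of results would have no interpretation fixed in advance.

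This is not a detail that a condensed article leaves to a fuller analysis plan. The article itself assigns the primary label to all four items and itself sets P < 0.05 as the criterion.

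**Working it through.** **1. The plan's own figure.** Inputs from Participants: 65% v 90%, two-sided alpha 0.05, power 0.90, equal groups. Pooled-variance formula without continuity correction:

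n = [z(0.975)·√(2·p̄·(1−p̄)) + z(0.90)·√(p1(1−p1) + p2(1−p2))]² / (p2−p1)²

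with p̄ = (0.65 + 0.90)/2 = 0.775:

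- first term: 1.960 × √(2 × 0.775 × 0.225) = 1.157
- second term: 1.282 × √(0.2275 + 0.0900) = 0.722
- n = (1.157 + 0.722)² / 0.0625 = 56.5, so 57 against the stated 56.

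The figure reproduces to within one patient. It is a calculation for **one** test at alpha 0.05. 56/0.80 = 70 matches the enrolment target.

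**2. Counting the tests.**

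| Variable | Method stated | Between-group tests |
|---|---|---|
| Attack frequency | repeated-measures ANOVA | 1 |
| Attack duration | repeated-measures ANOVA | 1 |
| VAS | repeated-measures ANOVA | 1 |
| SF-MPQ | repeated-measures ANOVA | 1 |
| Responders | chi-square, time not stated | 1 or 2 |
| **Total** | | **5 or 6** |

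This takes one group test per repeated-measures model. Group-by-time tests, or separate between-group tests at each visit, would add more. Five variables at two visits, all tested separately, gives 10 as an upper case.

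**3. Chance of at least one false positive** when no group difference exists and each test uses two-sided 0.05.

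- Independent tests: 1 − 0.95^k. For k = 5: 1 − 0.7738 = 22.6%. For k = 6: 1 − 0.7351 = 26.5%.
- Correlated tests: k normal test statistics with a common correlation ρ, by simulation (400,000 draws). The document gives no correlation, so the range is an assumption.

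| Tests | ρ = 0 | ρ = 0.5 | ρ = 0.7 | ρ = 0.9 |
|---|---|---|---|---|
| 5 | 23% | 18% | 15% | 10% |
| 6 | 26% | 21% | 16% | 11% |
| 10 (upper case) | 40% | 29% | 21% | 13% |

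**4. What splitting alpha would do to power.** The analysis is by intention to treat with last observation carried forward, so 70 per arm are analysed. Exact power of the two-sided test of proportions at 65% v 90%:

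| Alpha | 70 per arm |
|---|---|
| 0.05 (no split) | 96% |
| 0.01 (five variables) | 86% |
| 0.005 (ten tests) | 80% |

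These figures assume that 65% and 90% still hold once dropouts are included.

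**5. Does anything in the text designate one primary or control the others?**

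- The overall null hypothesis concerns the success probability only. No other test is made to depend on it.
- Tukey's procedure covers comparisons within groups. It does not adjust the between-group tests across outcomes.
- The sample size uses a responder proportion, without calling it the only primary or naming a time. Its definition (attack frequency) differs from that in the outcome list (migraine days).
- The 16-week collection is tied to the long-term effect and is not given primary status.

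**The case against.** The strongest reply is that the 5% level is not shown to be breached, because the protocol never says that one significant result is enough. If all five variables had to succeed, the chance of a false claim of overall success would be at most 5%. A reader might infer that the trial's error rate is simply far above 5%. The document does not support so flat a statement. The rate is undetermined, and it is inflated under the any-one-succeeds reading. That reading remains open, and nothing in the text closes it.

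A reader might also count ten tests and quote 40%. This does not fit the stated method, which compares the groups by repeated-measures ANOVA across times. No between-group test at each visit is stated for the continuous variables. Independence is also unlikely: frequency and the responder outcome both describe headache occurrence, VAS and SF-MPQ both measure pain, and carrying values forward ties the two visits together. So 40% is an upper case only.

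It is fair, too, that the sample size and the null hypothesis on success probability both point to responders as the main test. They make it the obvious candidate, but they neither designate it nor make the other tests conditional on it.

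Finally, one might conclude that dividing alpha would cripple the trial. Judged at 56 per arm the loss looks severe, but the planned analysis has 70 per arm, where splitting alpha is workable.

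**Conclusion.** The point stands in this form: five variables are labelled primary at two post-baseline times, each is held to P < 0.05, and no single primary, primary time, testing order or success rule is given. With about 5 to 6 between-group tests, and if one significant result suffices, the chance of at least one false-positive primary result is about 10% (correlation 0.9) to 26% (independence). That is roughly two to five times the stated 5%. The size rests on three assumptions: one group test per repeated-measures model, a common correlation in the range shown, and the any-one-succeeds reading. The defect itself, that the plan does not fix what counts as success, depends on none of them.

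**What to change.** By amendment before unblinding, name one primary outcome at one time and test it alone at two-sided 5%.

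- **Outcome.** The responder proportion is the natural choice: the sample size is built on it, and the stated null hypothesis concerns success probability.
- **Time.** Week 16 has support in Procedures. The sponsor may choose another single time, provided it is fixed in advance.
- **Definition.** Reconcile the two responder definitions (attack frequency in Participants, migraine days in Outcome measures). Otherwise the single primary would still have two versions.
- **The rest.** Make the other variables and the other time point secondary, or test them in a fixed sequence after the primary.

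The sample size does not change, because it was calculated for one test at alpha 0.05. The cost is that the demoted outcomes no longer support a stand-alone confirmatory claim.

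If several co-equal primaries are wanted, splitting alpha is a workable alternative at 70 per arm. Power on the responder outcome would then be 86% at alpha 0.01 or 80% at 0.005, below the planned 90%.

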### Intervention

In addition to rigorous methodological quality, both verum acupuncture and sham acupuncture interventions have been proposed based on a broad literature review and a consensus with acupuncture experts in Beijing Traditional Chinese Medicine Hospital. We conducted a pilot study with sample size 32 per group to confirm the efficacy of verum acupuncture compared with sham acupuncture. Besides, the interventions of two groups are based on the experiences of physicians who had worked with acupuncture for 20 years.

In the acupuncture group, 3 acupuncture sessions per week are carried out and placebo medicine is taken once a night for 4 weeks. In the control group, medicine (flunarizine) once a night for 4 weeks is given and 3 sham-acupuncture sessions are given per week. There are several common approaches of verum/sham acupuncture in both groups including: bilateral points; usage of disposable, sterile steel needles (0.32 mm × 40 mm); 10–12 needles used each time; skin disinfection with 75% alcohol; needles retention for 30 minutes and no moxibustion or electrical stimulation. Patients of both groups received 12 sessions of verum/sham acupuncture in 4 weeks.

The placebo medicines have exactly the same appearance as true medicines (flunarizine). Both Flunarizine and placebo are taken 10 mg once per night for the first 2 weeks and then 5 mg once per night for the next 2 weeks. All patients are allowed to treat acute headaches as need, but the type and dose of acute medications should be recorded in a headache diary.

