Acupuncture has been used for alleviating acute/chronic pain for thousands of years. The efficacy of acupuncture as abortive therapy for patients with migraine headaches has been proved by many studies [12]. Some studies suggested that sumatriptan was more effective than acupuncture at relieving headache [33]. Therefore, the purpose of this trial is not to discuss the efficacy of acupuncture as painkiller but evaluate the efficacy on preventing migraine attack. The results of our trial will be helpful to supply the evidence on the efficacy of acupuncture for migraine prophylaxis in China.

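### Attack duration, VAS and SF-MPQ stand as unranked primary outcomes although the article says the trial evaluates prevention of attacks and not pain relief, so a primary result could be positive with attack frequency unchanged

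*Protocol article*

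**What the plan says.** All places are in the protocol article.

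- **Outcome measures.** Four numbered items are introduced as primary measures of efficacy in migraine prophylaxis. They hold five quantities: attack frequency, attack duration, the responder proportion, "Visual Analogue Scale (VAS) to assess the severity of migraine pain", and the SF-MPQ. Secondary outcomes include "Intake of acute-medication". Assessments are before treatment, in the week of the last session, and 12 weeks after it.
- **Statistical analysis.** Significance is P < 0.05. The primary items are not ordered, and nothing says which must succeed.
- **Discussion.** The purpose is stated by contrast: "the purpose of this trial is not to discuss the efficacy of acupuncture as painkiller but evaluate the efficacy on preventing migraine attack". Shortly before that: "The efficacy of acupuncture as abortive therapy for patients with migraine headaches has been proved by many studies".
- **Intervention.** "All patients are allowed to treat acute headaches as need, but the type and dose of acute medications should be recorded in a headache diary". Needling is on a fixed schedule of 3 sessions a week for 4 weeks.
- **Background.** Lower severity and shorter duration are named with lower frequency among the goals of prophylactic therapy.
- **Participants.** The sample size rests on responders, defined there by a 50% or greater fall in attack frequency, assumed to be such that the proportion "would be 65% [14,15] in control group and 90% [16] in acupuncture group". The outcome list defines responders by migraine days instead.

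**The concern.** An attack that has a duration, a VAS score or an SF-MPQ score is an attack that took place. These three quantities can improve because attacks are milder or shorter while as many occur as before. The Discussion sets that kind of benefit apart from the question the trial asks, yet the outcome list gives it the same standing as fewer attacks. With no ranking, a significant VAS or SF-MPQ result can be reported as primary evidence of prophylaxis while attack frequency is unchanged.

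Two influences other than prevention act on these quantities. One is acute medication, which is taken after randomisation and whose use may depend on how well the prophylaxis works. The other is any direct analgesic effect of needling around the end-of-treatment assessment, which the article's own account of acupuncture as abortive therapy makes plausible. What is at stake is the meaning of a positive primary result, which could be prevention, pain relief or a mixture.

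**Working it through.** **1. What each primary quantity can show**

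| Primary quantity | Can improve with the number of attacks unchanged? |
|---|---|
| Attack frequency | No |
| Attack duration | Yes |
| Responder, at least 50% fewer migraine days | Yes: if attacks are as many but last half as many days, migraine days fall by 50% and the threshold is met |
| VAS | Yes |
| SF-MPQ | Yes |

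Three of the five (duration, VAS, SF-MPQ) describe only attacks that occurred. The responder outcome as worded in Outcome measures is mixed. As worded in Participants (attack frequency) it would count prevention alone.

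**2. Which way the other influences act**

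- *Acute medication.* Permission is the same in both arms; use need not be. If the less effective arm takes more, its scores fall and a true difference shrinks. If use differs for another reason, the shift could go either way. The article gives no SD for VAS, no effect of acute medication on a score and no expected use by arm. Neither size nor sign can be calculated.
- *Needling.* Sessions run 3 a week for 4 weeks, 12 in all. The end-of-treatment assessment falls in a week with sessions. The later one is 12 weeks after the last session, with no concurrent needling. A direct analgesic effect therefore bears mainly on the first of two post-baseline assessments, but the repeated-measures ANOVA in Statistical analysis carries that one into the group comparison.

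**3. Whether the sample size depends on the pain outcomes**

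Inputs from Participants: control 0.65, acupuncture 0.90, two-sided α = 0.05, power 0.90. The stated result is: "Based on 0.9 power to detect a significant difference (α = 0.05, two-sided), 56 patients are required for each group".

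Formula (pooled variance under the null, no continuity correction):

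n = [z(0.975)·√(2·p̄·(1−p̄)) + z(0.90)·√(p1(1−p1) + p2(1−p2))]² / (p2 − p1)²

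- p̄ = (0.65 + 0.90)/2 = 0.775
- First term: 1.960 × √(2 × 0.775 × 0.225) = 1.960 × 0.5906 = 1.1575
- Second term: 1.2816 × √(0.2275 + 0.0900) = 1.2816 × 0.5635 = 0.7221
- n = (1.1575 + 0.7221)² / 0.25² = 3.533 / 0.0625 = 56.5, so 57 after rounding up

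The stated 56 is reproduced to within one patient; power at 56 is 0.897. Enrolment of 70 corresponds to 1 − 56/70 = 20% dropout, and power with all 70 per group is 0.951. The calculation uses only the responder proportion. Making duration, VAS and SF-MPQ secondary therefore leaves the sample size as it is.

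**The case against.** The strongest reply is that severity and duration belong to prophylaxis. The Background says so, and patients care about them. On this reading the Discussion sentence, which follows a comparison with sumatriptan, only separates prophylactic from acute use of acupuncture. This stands in part. It justifies measuring the three outcomes and rules out calling them irrelevant. It does not settle whether they can alone carry a conclusion that the Discussion words as prevention of attacks.

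A second reply is that prevention is tested: frequency and responders are primary, the sample size rests on responders, and the only hypothesis stated concerns a success probability. All true. A reader might infer that the trial does not test its question at all, and the article does not support that. But nothing says that the prevention outcomes must succeed.

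Third, both arms have the same access to acute medication, and patients are masked with sham needling and matching placebo. A reader might infer a bias towards acupuncture, or an error rate inflated by a known amount. Neither follows. An error rate would need an assumed gap between arms in medicated attacks, and without a preventive difference the mechanism described above does not by itself produce one.

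Fourth, how acute medication enters the analysis may be left to a full protocol or analysis plan. That is accepted, and its absence from the article is not held against it. For the same reason I do not ask for pain scores taken before the first acute dose, since the article does not describe scoring per attack. Nor do I ask for duration split by whether acute medication was taken, since that would condition on a choice made after randomisation.

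**Conclusion.** The point holds as an inconsistency between the stated purpose and the status of three primary outcomes. Duration, VAS and SF-MPQ are offered as unranked primary proof of prophylaxis, while the Discussion limits the purpose to preventing attacks. A primary result could be declared positive with attack frequency unchanged. This follows from the text and needs no numerical assumption.

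No size can be put on any bias. Acute medication may push either way, and a direct effect of needling concerns mainly the end-of-treatment assessment. It would go too far to say that prevention goes untested, that the pain outcomes have no place, or that the design favours acupuncture by this route. The different responder definitions, attack frequency in Participants and migraine days in Outcome measures, add to the problem: the responder outcome as listed is not a count of prevented attacks either.

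**What to change.** 1. In Outcome measures, name one primary basis for the prophylaxis conclusion: the proportion of patients with at least 50% reduction in attack frequency, as already used for the sample size.
2. Replace migraine days by attack frequency in the listed responder definition, so that it agrees with Participants.
3. Move attack duration, VAS and SF-MPQ to secondary outcomes, and interpret them beside acute-medication intake by arm, for which type and dose are already recorded.
4. Reconcile the Background's goals of prophylaxis, the outcome list and the Discussion's statement of purpose, so that all three describe the same question.

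The cost is a change of wording. The 56 per group and the enrolment of 70 stay, nothing new is collected, and the acute-medication rule is untouched. The downside is that pain intensity and duration, which matter to patients, no longer count as primary results.
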